# A phase II study of personalized ultrafractionated stereotactic adaptive radiotherapy for palliative head and neck cancer treatment (PULS-Pal): a single-arm clinical trial protocol

**DOI:** 10.1186/s12885-024-13303-5

**Published:** 2024-12-21

**Keywords:** Head and neck cancer, Stereotactic body radiotherapy (SBRT), Personalized Ultrafractionated stereotactic adaptive radiotherapy (PULSAR), Palliative radiotherapy

## Abstract

**Background:**

Many patients with head and neck cancer are not candidates for standard of care definitive treatments though often require palliative treatments given the frequent symptoms associated with head and neck cancer. While existing palliative radiotherapy regimens can provide adequate symptom control, they have limitations particularly with respect to local control which is becoming more important as advances in systemic therapy are improving survival. Personalized ultrafractionated stereotactic adaptive radiotherapy (PULSAR) is a novel radiotherapy regimen which leverages advances in radiotherapy treatment technology and extended interfraction intervals to enable adaptive radiotherapy and possible synergy with the immune system. Additionally, HyperArc© (Varian Medical Systems, Inc.) radiotherapy planning software allows for safe dose-escalation to head and neck tumors.

**Methods:**

This single-arm phase II study will prospectively evaluate PULSAR with HyperArc© software for palliative treatment of head and neck cancer. Patients with de novo or recurrent, localized or metastatic, head and neck cancer who are ineligible for or decline standard of care definitive treatments are eligible for enrollment. Forty-three patients will receive an 11 Gray fraction of radiation every two weeks for a total of five fractions and dose of 55 Gy. Adaptive radiotherapy planning is permitted. A safety and feasibility evaluation will be performed after enrollment of the first fifteen patients whereby the trial will be closed if five or more patients experience a CTCAEv5.0 grade 3 or 4 or any patient experiences a grade 5 toxicity probably attributable to PULSAR during or within three months after its completion. The primary endpoint is one-year local head and neck tumor control. Secondary endpoints include safety, disease progression-free and overall survival, symptomatic impact, frequency of re-simulation and/or adaptive planning, and radiation dosimetry of PULSAR. Additionally, enrolled patients are permitted to receive cancer-directed systemic therapy, including immunotherapy, during PULSAR which may allow for the analysis of the safety and efficacy of this combination.

**Discussion:**

The PULS-Pal trial is the first prospective study of PULSAR with HyperArc© software for head and neck cancer. We hypothesize that this radiotherapy regimen will lead to improved local tumor control compared with historical controls in patients undergoing palliative radiotherapy for head and neck cancer.

**Trial registration:**

Clinicaltrials.gov identifier: NCT06572423. Date of registration: August 28th, 2024.

**Supplementary Information:**

The online version contains supplementary material available at 10.1186/s12885-024-13303-5.

## Background

A significant proportion of patients with de novo or recurrent head and neck cancer (HNC) will not be candidates for standard of care definitive treatment(s) [1–3], which includes a combination of surgery, radiation therapy, and/or systemic therapy, and in some cases, standard of care stereotactic body radiotherapy (SBRT). Common contraindications for standard definitive treatment for HNC include locally advanced disease not amenable to definitive treatment because of the anticipated morbidity with primary or salvage treatment, poor performance status, presence of metastatic disease, or patient treatment preferences [4, 5]. In such cases, locoregional palliative radiation therapy is often utilized given the frequent accompanying symptoms of HNC such as pain or difficulty breathing or eating [6], with the most common HNC palliative radiation therapy regimens being the RTOG-8502 regimen (“quad-shot”) [7–9] and SBRT [10]. While these current palliative radiation therapy options can provide adequate symptom improvement, there are some limitations with these regimens as well.

With quad-shot, there are logistic challenges for both providers and patients given the twice-daily treatments, albeit for just two days total. Moreover, typically multiple cycles are needed to achieve maximal symptomatic benefit, although only about 50% of patients will be able to complete three or more cycles at which point the palliative response rate of this regimen is significantly increased [8, 11–13]. Additionally, while newer radiation therapy techniques such as intensity modulated radiation therapy (IMRT) have been employed to enhance the quad-shot regimen, it represents an older radiation therapy practice which may not fully leverage more recent advances in radiation therapy technology. Regarding SBRT, there is the possibility for severe toxicity, minimization of which is important in the palliative setting, as well as efficacy concerns, particularly for larger tumors or in the re-irradiation setting [6, 14–16]. However, a main limitation across all palliative radiation therapy regimens is suboptimal local control. Local tumor progression negatively impacts symptoms and possibly overall survival given the frequency at which locoregional tumor progression causes death in patients with HNC [17–19].

Prospective data of SBRT for unresectable head and neck cancer has demonstrated one year local control rates of 60% in the re-irradiation setting [20]. In the de novo setting, prospective data are limited and primarily consist of SBRT for early-stage glottis cancer, though in small, retrospective series predominantly for palliative purposes and/or for patients who are not candidates for standard of care definitive therapy, the reported one year local control rates range from 69–87% [21]. However, not all patients will be eligible for standard of care SBRT in the definitive or palliative setting, for example because of tumor size or location near the carotid artery [22]. In such cases, a variety of other radiation regimens are often used, such as quad-shot, which generally have lower and/or less durable local control rates [23–25]. The durability of symptom and local control in this patient population is becoming more important as advances in systemic therapy, particularly immunotherapy, are improving patient survival [26–29].

Personalized ultrafractionated stereotactic adaptive radiotherapy (PULSAR) is a novel radiation therapy regimen in which large radiation doses are delivered in “pulses” over extended interfraction intervals, with typically several days to multiple weeks between each radiation fraction [30, 31]. The PULSAR technique is enabled by advances in SBRT and image-guided radiation therapy, and allows for possible adaptation of each subsequent fraction to the most current patient anatomy and tumor response. This not only permits adequate time passage for tumor shrinkage and subsequent adaptive radiation therapy re-planning to occur, but also a protracted SBRT course may be less toxic than the standard SBRT course typically delivered over 1–2 weeks given the additional time for normal tissue healing as well as smaller radiation fields with possible tumor shrinkage. To this end, the PULSAR paradigm may enable safer tumor dose escalation [32]. Similarly, advances in radiation planning and treatment delivery, specifically HyperArc© (Varian Medical Systems, Inc.) [33] technology, have permitted dose escalation with high conformity in HNC SBRT [15, 34]. Dose escalation has been found to be associated with improved locoregional control in HNC [35, 36], and thus the combination of PULSAR with HyperArc© technology may further improve the therapeutic ratio of palliative radiation therapy in this patient population. Even more so, it has been suggested that there may be a synergism between PULSAR and immunotherapy, and further exploration of this relationship is warranted, particularly in the clinical setting [37]. With the increased use of immunotherapy in patients with recurrent, unresectable, or metastatic disease [38], the potential complimentary relationship between PULSAR and immunotherapy may provide these patients with additional benefit.

In this context, PULSAR is an appealing option for patients requiring palliative radiation therapy for HNC. Given the potential efficacy, safety, symptomatic, and logistical benefits of this radiation regimen, we hypothesize that PULSAR delivered with HyperArc© technology will result in improved local control and similar or improved symptom relief while mitigating toxicity risk compared with existing palliative radiation regimens in patients with de novo or recurrent HNC who are not candidates for standard of care definitive treatment(s), including standard of care SBRT. To test this hypothesis, we will conduct a prospective clinical trial of PULSAR in this patient population. Because PULSAR is a newer technique, it has not yet been comprehensively studied, particularly in combination with HyperArc© technology. To our knowledge, there are currently nine early phase clinical trials prospectively evaluating PULSAR in some capacity (NCT 04677413, 04779489, 04786093, 04889066, 05021237, 05846646, 05846659, 06044857, 06359275), none of which are in HNC. Thus, validation of its safety and feasibility is first required prior to larger-scale prospective studies of efficacy in HNC. Herein, we propose an early safety and feasibility study of palliative PULSAR delivered with HyperArc© technology in patients with de novo or recurrent, localized or metastatic HNC who are ineligible for or decline standard of care definitive treatment(s).

HyperArc© radiation technology is a commercial tool that provides automated non-coplanar volumetric modulated arc therapy (VMAT) treatment planning. It was initially developed for intracranial stereotactic radiosurgery; however, it can be adapted for the treatment of HNC, and our institution has evaluated HyperArc© technology in HNC dosimetrically and prospectively with encouraging results [15, 34]. From a treatment planning perspective, HyperArc© allows for target dose escalation, which as noted above is correlated with improved locoregional control, while maintaining minimal head and neck organs-at-risk doses compared with more conventional VMAT SBRT [34]. From a clinical perspective, our institution recently completed patient accrual for a phase II trial of HyperArc© SBRT to 55 Gray in five every other day fractions for definitive treatment in previously radiated patients with recurrent HNC (NCT03892720). The initial report of this study found this intervention to be feasible, safe, and well tolerated with minimal treatment-related toxicity and favorable quality of life metrics. Additionally, unpublished analysis of this study found a one year local control rate of 85%, which is higher than existing prospective data of SBRT for recurrent, previously radiated HNC reporting a one year local rate of 60% [20]. These findings support the rationale for using HyperArc© treatment planning technology in this study.

## Methods/design

### Study design

This is a single-center (UCLA), single-arm, prospective phase II study with a safety lead-in. 43 subjects are planned. Each subject will receive the same PULSAR radiation therapy course as described below. The first 15 enrolled patients will be evaluated in the safety lead-in portion. If 5 or more of these 15 patients experience CTCAE v5.0 grade 3 or 4 or any patient experiences a grade 5 toxicity probably attributable to PULSAR during or within three months after completion of PULSAR, the study will be stopped for safety concerns; otherwise, the study will proceed, and those initial 15 patients will be included in the 43 subject sample. The trial schema is shown in Fig. 1.

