#### PULSAR treatment

Daily cone-beam CT will be obtained prior to radiation delivery to verify anatomic location and stability. Treatment will consist of 6, 10, or 15 MV photons directed at the PTV using HyperArc©’s automated non-coplanar VMAT technique. Patients will receive a total of 55 Gray in 5 fractions (biological effective dose with alpha/beta of 10: 115.5 Gray) to the PTV. Patients will receive each 11 Gray fraction of radiation every 14 +/−10 days. Treatment will be terminated early in cases of intolerable treatment-related toxicity, altered clinical context, or the patient declines further treatment.

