#### Safety lead-in/interim analysis

The study includes a safety lead-in portion, with formal evaluation on enrollment of the 15^th^ subject. The trial will be stopped if 5 or more patients in the safety lead-in portion experience a serious adverse event, defined as a CTCAE v5.0 grade 3 or 4 toxicity, or if any patient experiences a grade 5 toxicity probably attributable to the intervention during or within three months after completion of PULSAR.

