#### Sample size determination

Prospective data of SBRT for unresectable head and neck cancer has demonstrated 1 year local control rates of 60% in the re-irradiation setting [20]. In the de novo setting, prospective data are limited and primarily consist of SBRT for early-stage glottis cancer, though in small, retrospective series predominantly for palliative purposes and/or for patients who are not candidates for standard of care definitive therapy, the reported 1 year local control rates range from 69–87% [21]. However, in the palliative setting or patients unfit for definitive therapy, a variety of other radiation regimens are often used, such as the “Quad-Shot” regimen, which generally have lower and/or less durable local control rates [23–25]. From these data, we estimate the historic control group 1 year local control rate to be 65%.

For the study group, unpublished analysis of a recently closed phase II trial at UCLA of dose-escalated SBRT to 55 Gray for treatment of previously radiated, recurrent head and neck cancer demonstrated a 1 year local control rate of 85% (NCT 03892720). We therefore hypothesize that patients enrolled in this trial will have a similar 1 year local control rate. A sample size of 38 patients will achieve 80% power to detect a 20% difference in the 1 year local control rate between PULSAR (85%) and historic control (65%), using a two-sided one-sample exact binomial test, at 0.05 significance level. Considering that some patients may become ineligible/drop out after enrollment, the target sample size is determined to be at least 43 patients. The 15 patients in the safety lead-in portion will be included in the sample should the study proceed past this portion.

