#### Populations for analyses

##### Full Analysis Set (FAS)

All efficacy analyses will be performed on the Full Analysis Set (FAS) following the Intent-To-Treat (ITT) principle. Patients who were enrolled but did not receive study treatment are included in the FAS population.

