##### Safety Analysis Set (SAS)

All patients who received at least 1 fraction of radiation and for whom any valid post-baseline safety data are available will be included in the safety analysis set. When assessing safety and tolerability, summaries will be produced based on the safety analysis set. Patients are analyzed according to the actual treatment received.

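### The 5-of-15 toxicity stop rule is counted over enrolled patients, so each untreated patient among the 15 makes it less likely to trigger

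*Protocol article*

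**What the plan says.** Study design fixes the lead-in cohort by order of enrollment: "The first 15 enrolled patients will be evaluated in the safety lead-in portion". The condition for stopping then reads: "If 5 or more of these 15 patients experience CTCAE v5.0 grade 3 or 4 or any patient experiences a grade 5 toxicity". It concerns events judged to be probably due to the intervention, from the start of the course until three months after it ends, and the study stops when it is met. The Abstract and the Safety lead-in/interim analysis section also tie the evaluation to enrollment ("A safety and feasibility evaluation will be performed after enrollment of the first fifteen patients"; "with formal evaluation on enrollment of the 15^th^ subject").

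Elsewhere the article recognises that enrolled and treated patients are not the same group:

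- Full Analysis Set: "Patients who were enrolled but did not receive study treatment are included in the FAS population".
- Sample size determination, explaining the increase from 38 to 43: "Considering that some patients may become ineligible/drop out after enrollment".
- PULSAR treatment: "Treatment will be terminated early in cases of intolerable treatment-related toxicity, altered clinical context, or the patient declines further treatment".
- Safety Analysis Set: "All patients who received at least 1 fraction of radiation and for whom any valid post-baseline safety data are available will be included". The Safety analyses section uses this set.

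The stop rule is not linked to the Safety Analysis Set. The article does not say what happens to a lead-in place when its occupant is never treated.

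**The concern.** A toxicity rule measures the regimen only in people who received it. A patient who enrols and is never irradiated cannot have a toxicity attributable to PULSAR, yet on the stated wording is one of the 15. Because 5 is a fixed count, the observed rate among exposed patients needed to stop rises as the number exposed falls. The error from untreated patients runs one way, towards continuing.

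This matters because it is the only numerical limit on grade 3-4 toxicity in the document, and the Background says safety and feasibility must be validated before larger efficacy studies in this disease.

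**Working it through.** **The plan's own figures.** The article gives no operating characteristics for the 5-of-15 rule, so there is none to reproduce. The nearby sample size does reproduce. For an exact two-sided test of 65% against 85% with n = 38, the upper critical value is 31, the upper-tail error is 0.0205 and power is 79.9%, against the stated 80%. The step from 38 to 43 implies a loss of 5/43 = 11.6%.

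**Inputs.** Threshold of 5 and cohort of 15: Study design. True grade 3-4 rate p: not in the document; assumed between 20% and 50%. Number of the 15 actually exposed, m: not in the document; 15, 14 and 13 are shown.

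**Formula.** With independent patients and no events among the untreated,

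P(stop) = 1 − Σ (j = 0 to 4) C(m, j) p^j (1 − p)^(m − j).

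Example, m = 15 and p = 0.30: the five terms are 0.0047, 0.0305, 0.0916, 0.1700 and 0.2186. They sum to 0.515, so P(stop) = 48.5%.

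| Exposed, m | Observed rate needed, 5/m | p = 20% | p = 30% | p = 40% | p = 50% |
|---|---|---|---|---|---|
| 15 | 33.3% | 16.4% | 48.5% | 78.3% | 94.1% |
| 14 | 35.7% | 13.0% | 41.6% | 72.1% | 91.0% |
| 13 | 38.5% | 9.9% | 34.6% | 64.7% | 86.7% |

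One untreated patient costs 48.5 − 41.6 = 6.9 percentage points at 30% and 78.3 − 72.1 = 6.2 at 40%. Two cost 13.9 and 13.6.

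**Partly dosed patients.** These remain at risk, so zero risk is the wrong model for them. Suppose, purely as an assumption, that k of the 15 carry half the risk. Then

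P(stop) = Σ (j = 0 to k) C(k, j) (p/2)^j (1 − p/2)^(k − j) × P(at least 5 − j events among 15 − k at rate p).

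For k = 2 this gives 41.5% at p = 30% and 71.8% at 40%, close to the effect of one untreated patient. For k = 3 it gives 38.1% and 68.1%. Patients who stop because of a qualifying toxicity supply events and do not dilute the rule.

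**The case against.** The strongest reply is that this presses one word in a condensed article. The sentence just before the lead-in definition has every subject receiving the same course. The Safety analyses section uses the treated-only set. The Abstract and interim-analysis wording can be read as timing the evaluation rather than defining its denominator. Replacement and evaluability rules are details that a full protocol commonly holds. Part of this stands: silence on replacement is not a rule against it, and a reader should not infer that nobody will be replaced or that untreated patients will be declared to have tolerated the regimen. But the denominator is not left open: Study design states it, by enrollment. Applying the Safety Analysis Set only at the analysis stage would not repair it either. If the cohort closes at 15 enrolled and 13 are in that set, the fixed count still demands 5 of 13.

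A second reply is that other safeguards exist. Any grade 5 event probably attributable to PULSAR stops the trial, and that trigger has no denominator to dilute. The DSMB reviews each SAE monthly. Both limit the consequences, but neither restores the sensitivity of the grade 3-4 count.

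A third reply concerns size, and here stronger readings should be resisted:

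- The 5/43 allowance would imply 15 × 5/43 = 1.7 lost lead-in patients. It was set for the one-year endpoint and covers all ineligibility and dropout, including patients lost after the toxicity window. It is not an estimate of untreated lead-in patients.
- Scenarios with only 8 or 10 informative patients would treat partly dosed patients as having no risk.
- The completion figure of about 50% in the Background concerns repeated quad-shot cycles, a different regimen.
- The Background reports minimal treatment-related toxicity with 55 Gy in five fractions. That was on an every-other-day schedule in previously irradiated patients, so it neither supports nor excludes the rates assumed here.

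**Conclusion.** The point holds as a defect in a stated rule. The stop-rule cohort is defined by enrollment, the article itself allows for enrolled patients who are never treated, and its own safety set is defined by treatment. Followed literally, one or two untreated patients among the 15 lower the chance of stopping by about 6 to 14 percentage points at assumed true rates of 30% to 40%.

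These sizes rest on assumed toxicity rates, on independence between patients and on an assumed number untreated; the document supplies neither the rates nor the number. The point is confined to the grade 3-4 limb. Partly dosed patients add to the effect by a smaller amount that cannot be fixed from the document. The material does not support a claim that the lead-in would rest on far fewer than 15 exposed patients.

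**What to change.** In Study design, define the lead-in as the first 15 patients in the Safety Analysis Set, and state that the place of any untreated patient goes to the next enrolled patient within the planned 43. Keep the threshold of 5. Bring the Abstract and the Safety lead-in/interim analysis section into line. Report fractions received and follow-up completed for each lead-in patient, so that partial exposure is visible.

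Do not require completion of all five fractions while also keeping every patient with an event. That would remove event-free patients who stopped early and bias the observed toxicity rate upward. Any further minimum exposure or follow-up for evaluability is for the sponsor to set, and it should be set before the lead-in reads out, so that the denominator is not chosen after events are known.

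The cost is wording and a slightly later readout, with no increase in the total of 43. At the anticipated two to four enrollments a month, replacing one or two patients adds between 1/4 = 0.25 and 2/2 = 1 month of accrual. The rule would also stop somewhat more often at low true rates (16.4% rather than 9.9% at 20%, against 13 exposed), which is simply how 5 of 15 behaves when all 15 are treated.

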**Fig. 1 Fig1:**
[figure not shown]
Trial Schema

